# Efficacy and safety assessment of different dosage of benznidazol for the treatment of Chagas disease in chronic phase in adults (MULTIBENZ study): study protocol for a multicenter randomized Phase II superiority clinical trial

**DOI:** 10.1186/s13063-020-4226-2

**Published:** 2020-04-15

**Keywords:** Chagas disease, Benznidazole, Therapeutic, Multicenter study, Clinical trial

## Abstract

**Background:**

Chagas disease (CD) continues to be a neglected infectious disease with one of the largest burdens globally. Despite the modest cure rates in adult chronic patients and its safety profile, benznidazole (BNZ) is still the drug of choice. Its current recommended dose is based on nonrandomized studies, and efficacy and safety of the optimal dose of BNZ have been scarcely analyzed in clinical trials.

**Methods/design:**

MULTIBENZ is a phase II, randomized, superiority, double-blind, multicenter international clinical trial. A total of 240 patients with *Trypanosoma* CD in the chronic phase will be recruited in four different countries (Argentina, Brazil, Colombia, and Spain). Patients will be randomized to receive BNZ 150 mg/day for 60 days, 400 mg/day for 15 days, or 300 mg/day for 60 days (comparator arm). The primary outcome is the efficacy of three different BNZ therapeutic schemes in terms of dose and duration. Efficacy will be assessed according to the proportion of patients with sustained parasitic load suppression in peripheral blood measured by polymerase chain reaction. The secondary outcomes are related to pharmacokinetics and drug tolerability. The follow-up will be 12 months from randomization to end of study participation. Recruitment was started in April 2018.

**Conclusion:**

This is a clinical trial conducted for the assessment of different dose schemes of BNZ compared with the standard treatment regimen for the treatment of CD in the chronic phase. MULTIBENZ may help to clarify which is the most adequate BNZ regimen in terms of efficacy and safety, predicated on sustained parasitic load suppression in peripheral blood.

**Trial registration:**

ClinicalTrials.gov, NCT03191162. Registered on 19 June 2017.

## Introduction

Chagas disease (CD) is a neglected parasitic infection caused by the protozoan *Trypanosoma cruzi*. It is endemic in the American continent, and according to the latest estimates, it affects around 6 million people. Thirteen percent of the Latin American population remains at risk of contracting the infection, which is transmitted to humans by Triatominae insects [1]. CD has also become a rising health problem in nonendemic countries because of international migration, and nonvectorial transmission can occur trhough blood transfusion, organ transplant, and congenital infection [2, 3]. In addition, orally transmitted CD has been detected in endemic areas because of food carrying either infected Triatominae insects or their feces [4].

After malaria and schistosomiasis, CD represents the third largest parasitic disease burden globally, with more than 15,000 deaths attributed directly to chronic Chagas cardiomyopathy (CCM) annually. CCM is the main complication in the chronic phase of CD, and it develops in approximately 30% of patients chronically infected with *T. cruzi* [1]. Moreover, it is the most common form of nonischemic cardiomyopathy in Latin America [5, 6].

Currently, there are only two available drugs to treat CD: nifurtimox and benznidazole (BNZ). Of these two, BNZ is the one most studied and most often used as a treatment. However, current schemes of this treatment have some limitations. On the one hand, it has a limited efficacy based on seroconversion (around 50–80% in the acute phase of the disease and 8–20% in the chronic phase) [7]. Another important limitation is the high rate of adverse events (AEs) when using these drugs. The incidence of AEs related to BNZ varies from 40–50% up to 98%, and around 15% of these patients have to definitively stop the treatment for this reason, with the rate even higher in patients treated with nifurtimox [8–10]. The most commonly observed AEs are hypersensitivity (rash, fever, generalized edema, lymphadenopathy, myalgia, and arthralgia), gastrointestinal disorders, bone marrow toxicity (neutropenia and thrombocytopenic purpura), and peripheral polyneuropathy [9]. Current knowledge about the BNZ toxicity mechanisms is scarce because the main studies have focused on the clinical aspects of these AEs [10]. Our group recently carried out an analysis of the cytokine profile and human leukocyte antigen (HLA) classes I and II of patients who were treated with BNZ, and we found a higher treatment discontinuation rate due to skin hypersensitivity AEs in patients who had the HLA-B*3505 allele [11].

Moreover, another drawback of the studies assessing the efficacy of BNZ in chronic CD is the lack of a biomarker to define the cure of disease. Currently, the cure criteria are negative seroconversion of two serologic assays against different antigens, but it usually takes several years after an effective treatment, precluding its use in clinical trials. In addition, detection of *T. cruzi* DNA in peripheral blood cannot be used to define cure, because a negative result does not mean absence of the infection; however, in recent years, it has become an important tool used to identify therapeutic failure when the result remains positive after completed treatment [8].

Antitrypanosomal treatment is always recommended for acute and congenital CD, reactivated CD infections, and chronic CD in individuals younger than 18 years of age [3, 12]. Despite the limitations of treatment of chronic CD in adults, international guidelines recommend treatment with either BNZ or nifurtimox in patients under 50 years old with nonestablished cardiac complications [13, 14]. This is based mainly on the lower long-term clinical progression observed in patients treated with BNZ after a mean follow-up of 10 years, the parasite persistence and concomitant chronic inflammation underlying CCM, and the prevention of vertical transmission to children born by infected women and treated before pregnancy [3, 15]. Results of a systematic review and meta-analysis showed little benefit of the treatment, and the BENEFIT (Evaluation of the Use of Antiparasital Drug [Benznidazole] in the Treatment of Chronic Chagas’ Disease) trial found no statistically significant reduction of cardiac clinical impairment in patients with moderate to severe cardiomyopathy [16, 17]. Treatment should be individualized for patients older than 50 years of age and for patients with comorbidities [3].

### BNZ dosing and duration

Currently, the recommended BNZ dosage and duration regimen for CD treatment is 5–7 mg/kg/day for 60 days. This recommendation is based on studies carried out in the 1970s [18]. However, nowadays, both the dose and duration of treatment are under discussion, predicated in findings from CD murine models, pharmacokinetic (PK)/pharmacodynamic studies, and studies in patients who discontinued the treatment. On this basis, it seems clear that BNZ dose may be optimized.

#### Lower dose

Two population PK studies have shown through mathematical models that lower dosage with the same duration would have the same efficacy [19, 20]. One of them [19] was carried out in children and the other in adults [20]. In the pediatric study, children were treated with a standard dose of BNZ. Although significantly lower concentrations of the drug were achieved compared with those reported in adults, the treatment was effective in all patients who completed the treatment course. Moreover, data from a second study carried out in adults revealed that a dose of 5 mg/kg/day might lead to overexposure in the majority of patients and that a BNZ dose of 2.5 mg/kg/day is enough to adequately keep BNZ trough plasma concentrations within the recommended target range according to previous PK studies [21, 22].

#### Higher dose

Recent in vitro assays that quantify the time necessary to eliminate the parasites (time-to-kill assays) showed that nitroheterocyclic compounds such as BNZ are dose-dependent [23]. In fact, treatment schemes with a higher-than-standard dose of BNZ (400 mg daily) with the same duration already have been used (STOP-CHAGAS [A Study of the Use of Oral Posaconazole in the Treatment of Asymptomatic Chronic Chagas Disease] study), without observing a higher proportion of side effects [24]. Furthermore, another study of 54 patients treated with BNZ tried to establish a correlation between the serum concentrations of the drug and the appearance of AEs. Fifty-three patients (98%) experienced at least one AE during follow-up, but no relationship was found between the drug serum concentration and the occurrence of AEs [25].

#### Shorter regimens

Finally, regarding the duration of treatment, recent studies in animal models have shown that shorter schemes (25% of standard duration) achieve the same cure rate [26]. This is under assessment in other clinical trials [27, 28], but findings of one study showed an important cure rate in patients who had to abandon the treatment due to severe adverse events (SAEs) [29].

## Methods/design

The MULTIBENZ study (Evaluation of Different Benznidazole Regimens for the Treatment of Chronic Chagas Disease; ClinicalTrials.gov, NCT03191162) is a phase II, superiority, parallel-arm, randomized, double-blind, multicenter international clinical trial assessing the efficacy and safety of three different BNZ dose schemes for the treatment of CD in chronic phase. It will be carried out in four different countries: Argentina, Brazil, Colombia, and Spain (protocol version V1/05-12-2016).

### Outcomes and endpoints

The primary objective of MULTIBENZ is to evaluate the efficacy of different BNZ regimens at 12 months after randomization in patients with CD in the chronic phase. The primary efficacy outcome is defined as the proportion of patients with sustained parasitic load suppression in peripheral blood measured by polymerase chain reaction (PCR) during the first 12 months of follow-up after randomization.

The secondary objectives are to evaluate the parasitic kinetics by detecting parasitic DNA measured by PCR in peripheral blood at different time points (weeks 1, 2, 4, and 8 during the treatment period and in the fourth, sixth, and eighth months after the start of treatment), to evaluate the serological response by enzyme-linked immunosorbent assay (ELISA) methods at the end of follow-up (month 12), to assess the tolerability and safety of the different BNZ regimens, to correlate BNZ levels with the therapeutic response and AEs, to correlate the presence of HLA-B*3505 with the presence of severe AEs, and to correlate the different discrete typing units of *T. cruzi* with the therapeutic response.

#### Primary endpoints

The primary endpoint is parasitologic response, defined as maintained negative qualitative PCR results during the 12-month follow-up period. For efficacy assessments, the end of treatment of each treatment arm will be defined in accordance with the duration of the treatment regimen. Incidence and severity of AEs and those leading to treatment discontinuation will also be recorded.

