### Randomization and follow-up

Patients are randomly assigned to receive BNZ 150 mg/day for 60 days, 400 mg/day for 15 days, or the standard scheme of 300 mg/day for 60 days. Because this is a double-blind trial, investigators and all sponsor staff will not be aware of the treatment allocation and randomization list until the end of the trial. Double-blinding will be adopted for all trial arms. Patients will be randomized 1:1:1, and randomization will be done via a remote and interactive response system, according to a predefined list. To avoid bias, randomization will be centralized and concealed. The treatment groups will be allocated on day 1 on the basis of a balanced block randomization, taking into account the country. Each patient will be assigned an identification code that will correspond to the trial kit number allocated to the patient. The label will indicate the trial number and the number of the kit, but it will not indicate the treatment designation.

Scheduled follow-up visits will occur at 7, 15, 28, and 60 days and up to 4, 6, 8, and 12 months after initiation of treatment. More information is provided in Fig. 1.

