### Sample size and data analysis

For the sample size calculation, we considered a superiority design for two-sample comparison of proportions. We hypothesize a reduction of 50% of the total number of patients who either have a positive PCR result during follow-up or have to discontinue the treatment due to AEs, has been taken into account as a hypothesis. It is estimated that in the standard arm of treatment, 40% of patients will be evaluated as treatment failures according to the intention-to-treat principle.

Given the expected proportions in every group and given that we plan two pairwise comparisons for a power of 80% and a type I error of 0.05, the total number of patients that should be included in the study is 240, which will comprise 60 participants per country.

The categorical data will be presented as absolute numbers and proportions, and the continuous variables will be expressed as means and standard deviations when normal distribution is demonstrated (using the Kolmogorov-Smirnov test) or as medians and interquartile ranges when it is not.

For comparison of the distribution of categorical variables, the χ^2^ test or Fisher’s exact test will be used, and the Mann-Whitney *U* test or Student’s *t* test will be used for continuous variables, respectively, depending on the presence or not of normal distribution.

A comparative analysis of the main clinicoepidemiological variable among the three groups will be carried out. The primary efficacy analysis will be the comparison of the proportion of patients with sustained parasitologic clearance of each treatment arm compared with the standard arm of treatment. The time until the first positive PCR result for *T. cruzi* will be evaluated by Kaplan-Meier survival analysis with the log-rank test for significance.

The proportion of patients with SAEs and/or AEs leading to treatment discontinuation will be described per trial arm and by System Organ Class (using preferred terms defined by MedDRA 13.1), according to the National Cancer Institute’s Common Terminology Criteria for Adverse Events (version 4.03). Incidence rate and 95% confidence interval will be presented per trial arm for SAEs and AEs per category, along with the most frequent AEs.

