#### PCR

Laboratories included in the project will carry out the same reverse transcriptase (RT)-PCR protocol following the instructions included in the laboratory manual agreed among all of them. To carry out this technique, 5 ml of whole blood will be collected and mixed with 5 ml of guanidine hydrochloride 6 M–ethylenediaminetetraacetic acid 0.2 M for a minimum of 72 h at room temperature. Three DNA extractions will be performed using the manual column method (High Pure PCR Template Preparation Kit; Roche Diagnostics, Mannheim, Germany), except in Spanish centers (Vall d´Hebron University Hospital and Ramón y Cajal University Hospital) where DNA extraction will also be done in triplicate using an automated extraction method (NucliSens easyMAG, bioMèrieux, Marcy l’Etoile, France).The consensual PCR protocol consists of a real-time multiple PCR (Duffy et al. 2013) [30] that allows the amplification of a *T. cruzi* satellite DNA region and a linearized recombinant plasmid used as an internal amplification control. The RT-PCR will be carried out in duplicate from each of the extractions. At least one amplification of the six performed with an amplification cycle (cycle threshold) of *T. cruzi* below 40 and a correct value of Internal Amplification Control (IAC) will be interpreted as positive. To be correct, the values of the IAC must meet Tukey’s criteria.

To assess the homogeneity of the results obtained by the different laboratories, a harmonization panel consisting of ten tubes containing blood with uninfected guanidine and infected with 1, 10, and 100 parasitic equivalents per milliliter of *T. cruzi* strains TcV and TcVI was processed. The samples were processed blindly by the different laboratories, and the results were evaluated by an external center in charge of providing the panel and analyzing the results (Instituto de Investigaciones en Ingeniería Genética y Biología Molecular, Buenos Aires, Argentina). On the other hand, and following the same work scheme, four external quality control panels will be analyzed during the study period.

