	Selection visit (from − 3 months to day 0)	Baseline visit (day 0)	Treatment visit (day 7 ± 2)	Treatment visit (day 15 ± 3)	Treatment visit (day 28 ± 4)	End of treatment visit (day 60 ± 7)	Side effect visit (not scheduled)	Follow-up visit (months 4, 6, and 8)	Final visit (month 12)
**Informed consent**	x								
**Demographic data**	x								
**Pathological background**	x								
**Toxic habits**	x								
**Chagas disease history**	x								
**Concomitant medication**	x	x	x	x	x	x	x	x	x
**Directed anamnesis**	x	x	x	x	x	x	x	x	x
**Physical examination**	x	x	x	x	x	x	x	x	x
**Pregnancy test**		x							
**Hematology**	x		x	x	x	x	x		
**Biochemistry**	x		x	x	x	x	x		
**HLA**	x								
**Chest x-ray**	x								
**EKG**	x								
**PK**				x		x	x		
**Serology**	x								x
**PCR**	x		x	x	x	x		x	x
**Other complementary tests**	x								
**Adverse events**		x	x	x	x	x	x		
**Randomization**	x								
**Study medication**		x	x	x	x	x			

*Abbreviations: EKG* Electrocardiogram, *HLA* Human leukocyte antigen, *PCR* Polymerase chain reaction, *PK* Pharmacokinetics

During this phase, any patient may consult spontaneously for the eventual occurrence of any AE. The decision to interrupt the treatment will be according to the discretion of the clinical researcher treating the patient, taking into account the severity, intensity, and extent of these AEs. In addition, the patient may decide unilaterally to suspend or not the medication at any time during the treatment period.
4.**Follow-up phase**

Once the patient has taken the last dose of treatment, which may be at the end of the therapeutic scheme (day 60), when a severe AE that obliges the patient to suspend the medication occurs, or when the patient unilaterally decides to suspend the medication, this phase will begin, and it will last up to 12 months after randomization. The visit schedule of this phase is presented in Table 3.

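### The primary PCR window is defined in three conflicting ways; on the reading the endpoint section suggests, the 15-day arm is scored on two more PCR visits than the 60-day arms

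*Protocol article*

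**What the plan says.** Patients receive "BNZ 150 mg/day for 60 days, 400 mg/day for 15 days, or the standard scheme of 300 mg/day for 60 days" (Randomization and follow-up). PCR is marked in Table 3 at the same times in every arm: days 7, 15, 28 and 60, then months 4, 6, 8 and 12. The last visit is 12 months after randomization in all arms.

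The window for the primary endpoint is described in three ways:

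- **Outcomes and endpoints:** sustained suppression "during the first 12 months of follow-up after randomization".
- **Primary endpoints:** "maintained negative qualitative PCR results during the 12-month follow-up period", followed by the statement that for efficacy assessments "the end of treatment of each treatment arm will be defined in accordance with the duration of the treatment regimen".
- **Secondary endpoints and Study organization:** weeks 1, 2, 4 and 8 are assigned to the treatment period and months 4, 6 and 8 to the follow-up period, without distinguishing arms. The treatment phase is said to last 60 days whichever arm is assigned. The follow-up phase opens as follows: "Once the patient has taken the last dose of treatment, which may be at the end of the therapeutic scheme (day 60"; it opens earlier for patients who stop early.

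The PCR section sets the positivity rule for a visit: "At least one amplification of the six performed" is enough. The time to first positive PCR "will be evaluated by Kaplan-Meier survival analysis with the log-rank test for significance"; no time origin is given.

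**The concern.** The three descriptions select different PCR visits and so can give different primary results from the same data. Read literally, a window from randomization counts on-treatment samples from day 7, although detectable parasite DNA is an inclusion criterion and every patient starts positive. A window from each regimen's end treats the arms unequally: days 15 and 28 fall inside it for the 15-day arm, while the 60-day arms are still on drug at those visits and the samples are not scored.

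One positive visit breaks the all-negative rule, and one positive amplification of six makes a visit positive. An arm with more scored visits therefore has more chances to fail. At stake is the comparison of the 15-day regimen with standard treatment, one of the two planned pairwise comparisons.

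**Working it through.** **1. The plan's own figure.** Inputs from Sample size and data analysis: 40% failure in the standard arm, halved to 20%; 80% power; type I error 0.05; 240 patients in total, which at 1:1:1 is 80 per arm. Two-sided 0.05 without adjustment or continuity correction gives 82 per arm (246) with pooled variance, 79 (237) with unpooled variance and 81 (243) with the arcsine formula. The plan's 240 is reproduced to within 3%. With pooled variance, power at 80 per arm is 79.4%. The window problem does not affect this calculation.

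**2. PCR visits scored under each description** (patients who complete treatment):

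| Window opens at | 15-day arm | 60-day arms |
|---|---|---|
| Randomization | 8 (days 7, 15, 28, 60; months 4, 6, 8, 12) | 8 (same) |
| End of each regimen, that sample counted | 7 (days 15, 28, 60; months 4, 6, 8, 12) | 5 (day 60; months 4, 6, 8, 12) |
| End of each regimen, that sample not counted | 6 (days 28, 60; months 4, 6, 8, 12) | 4 (months 4, 6, 8, 12) |
| End of a 60-day phase in all arms, day 60 not counted | 4 | 4 |

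The two middle rows both differ by two visits. The difference would be one only if day 15 were excluded and day 60 included.

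**3. Direction.** Failure means at least one positive among the scored visits. Adding visits to that set can leave the probability unchanged or raise it, never lower it.

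**4. Size.** The document gives no per-visit positivity, so what follows is assumption, shown as a range.

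*(a) Extra visits only detect uncured patients.* Let f be the uncured fraction and s the per-visit sensitivity in uncured patients, with visits independent. The excess for 6 against 4 visits is f × [(1−s)^4 − (1−s)^6].

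| s | f = 40% | f = 20% |
|---|---|---|
| 20% | 0.4 × (0.4096 − 0.2621) = 5.9 points | 2.9 points |
| 50% | 0.4 × (0.0625 − 0.0156) = 1.9 points | 0.9 points |
| 70% | 0.3 points | 0.15 points |
| 90% | about 0 | about 0 |

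For 7 against 5 visits and f = 40%, the excess is 4.7 points at s = 20% and 0.9 at s = 50%.

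*(b) Isolated positives are common.* Let every visit have the same independent chance q of being positive, set so that a 60-day arm fails at 20%.

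- 4 visits: q = 1 − 0.8^(1/4) = 5.4%. Over 6 visits, failure is 1 − 0.8^(6/4) = 28.5%, an excess of 8.5 points.
- 5 visits: q = 1 − 0.8^(1/5) = 4.4%. Over 7 visits, failure is 1 − 0.8^(7/5) = 26.8%, an excess of 6.8 points.

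Power against 40% at 80 per arm falls from 79% to 34% (6 against 4) or 42% (7 against 5). This is an upper-range model: it treats visits as independent and all failures as PCR failures, whereas the planned failure rate also includes discontinuations for adverse events.

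*(c) False positives alone.* Seven visits are 42 amplifications and five are 30. At an assumed 0.1% per amplification, the chance of at least one is 1 − 0.999^30 = 3.0% against 1 − 0.999^42 = 4.1%. At 0.5% it is 14% against 19%.

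**The case against.** The strongest objection is that the Primary endpoints section never says the window starts at end of treatment. It says only how end of treatment is defined for efficacy. The Secondary endpoints and Study organization sections support a 60-day treatment period in every arm and hence equal visits. The imbalance arises under only one of the three descriptions. This stands, so the point is an unresolved conflict with a biased reading, not a design shown to be biased. It does not remove the point: no other purpose of the efficacy sentence is apparent, and the article itself states the competing windows. This goes beyond detail left to a fuller document.

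Second, the Discussion treats detectable parasite DNA after treatment end as therapeutic failure. A day-28 positive in the 15-day arm would then be a failure by the trial's own criterion. Counting from each regimen's end is a defensible choice of question, so extra failures need not come from ascertainment alone. That is a reason to keep this version as a sensitivity analysis. It still leaves the arms with unequal numbers of tests.

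A reader might go further in three directions that the documents do not support.

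- **A large power loss taken as established.** If 5%, 10% or 20% of otherwise negative short-arm patients had an isolated early positive, a true 20% failure would be measured as 24%, 28% or 36%, and power would fall to 58%, 36% or 8%. The arithmetic is right, but no such proportions are given, and the model counts only patients who are positive early and negative ever after.
- **A Kaplan-Meier analysis in which the 60-day arms cannot fail before day 60.** No time origin is stated, so this is conjecture; what can be said is that the origin needs fixing.
- **A spurious claim of superiority for the 15-day arm.** The error runs the other way.

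**Conclusion.** The point holds as a conflict in the definition of the primary endpoint. If the efficacy sentence governs, as its wording suggests, the 15-day arm is scored on two more PCR visits, and the direction is certain: its failure rate can only be raised. The size is not known. It runs from about zero when per-visit sensitivity in uncured patients is high, through 1.9 points at 50% and 5.9 points at 20% (40% uncured, 6 against 4 visits), to 7-8 points or more if isolated positives are frequent. The Introduction says that a negative PCR does not mean absence of infection, so high per-visit sensitivity cannot be presumed.

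The effect is reduced power, and an understated result, for the 15-day regimen against standard. The 150 mg against 300 mg comparison has equal 60-day durations and is untouched. This is worth settling before unblinding, but it is not a demonstrated bias of known size.

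**What to change.** Reconcile Outcomes and endpoints, Primary endpoints, Secondary endpoints, and the treatment-phase and follow-up-phase text of Study organization, so that one window is stated. Define the primary endpoint on one set of PCR visits that falls after the scheduled end of active drug in every arm: negative at months 4, 6, 8 and 12. Keep the version counted from each regimen's end as a prespecified sensitivity analysis. State one common time origin, and the same visits, for the Kaplan-Meier and log-rank analysis.

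The cost is a change of wording before unblinding; no samples or visits are added. There are two downsides. An isolated early positive in the 15-day arm no longer counts in the primary endpoint, though it stays in the sensitivity analysis and in the secondary clearance endpoints at weeks 1 to 8. Time since last dose also still differs at each visit: taking month 4 as day 120, it is about 120 − 15 = 105 days after the last dose in the 15-day arm and 120 − 60 = 60 days in the others. The change equalises the number and calendar timing of tests, not the time off drug.
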